## Abstract

**Introduction:**

Falls are increasingly recognised for their ability to herald impending health decline. Despite the likely susceptibility of postsurgical patients to falls, a detailed description of postoperative falls in an unselected surgical population has never been performed. One study suggests that preoperative falls may forecast postoperative complications. However, a larger study with non-selected surgical patients and patient-centred outcomes is needed to provide the generalisability and justification necessary to implement preoperative falls assessment into routine clinical practice. The aims of this study are therefore twofold. First, we aim to describe the main features of postoperative falls in a population of unselected surgical patients. Second, we aim to test the hypothesis that a history of falls in the 6 months prior to surgery predicts postoperative falls, poor quality of life, functional dependence, complications and readmission.

**Methods and analysis:**

To achieve these goals, we study adult patients who underwent elective surgery at our academic medical centre and were recruited to participate in a prospective, survey-based cohort study called Systematic Assessment and Targeted Improvement of Services Following Yearlong Surgical Outcomes Surveys (SATISFY-SOS) (NCT02032030). Patients who reported falling in the 6 months prior to surgery will be considered ‘exposed.’ The primary outcome of interest is postoperative falls within 30 days of surgery. Secondary outcomes include postoperative functional dependence, quality of life (both physical and mental), in-hospital complications and readmission. Regression models will permit controlling for important confounders.

**Ethics and dissemination:**

The home institution's Institutional Review Board approved this study (IRB ID number 201505035). The authors will publish the findings, regardless of the results.

Strengths and limitations of this studyPublishing protocols for observational studies is not routine practice, so this protocol sets a rigorous precedent for similar studies.This is the first trial to describe postoperative falls and the association between preoperative falls and postoperative falls, poor quality of life and functional dependence.The study population is both large (∼8000 patients) and non-selected.The enrolment rate of eligible patients is 65%, baseline survey response is 92% and 30-day survey response is 55%. Non-participation at any of these stages may introduce bias.Variables were not always available or derived from a validated tool.

## Introduction

This protocol followed published guidelines for protocols for observational studies, along with the Strengthening the Reporting of Observational Studies in Epidemiology (STROBE) checklist for cohort studies (see online supplementary material for the STROBE checklist).^1^
^2^ For maximum transparency, we also added a limitations section. This protocol is V.01, written on 16 February 2016. The study will start after the protocol is accepted for publication (estimated study dates March 2016 to June 2016). See the Background section for literature review and justification for this study.

10.1136/bmjopen-2016-011570.supp1Supplementary data

## Background

### Literature search and review

In preparation for this study, a systemised review of the literature was performed on preoperative and postoperative falls.^3^ This review showed that a limited number of studies on postoperative falls have been conducted, and the few that have been performed mostly study orthopaedic and elderly populations. While one study characterised postoperative falls in all surgery types, it was limited by its retrospective design, inpatient time period and exclusively male population.^4^ Another study suggested that most postoperative falls may be surgery related, especially in the first weeks following surgery. However, it only tracked falls that resulted in hospital care, and its follow-up period was limited to 90 days.^5^

Regarding the second aim of predicting postoperative outcomes, our systemised review identified just one paper that studied the association between preoperative falls and postoperative complications and readmission.^6^ However, the sample size was small (235), and the population included only men over 65 undergoing cardiac or colorectal surgery at a Veterans Affairs hospital. Using Medical Subject Heading (MeSH) terms of ‘accidental falls’, ‘postoperative period’ and each outcome, a thorough PubMed search was also performed to identify other relevant papers linking falls, surgery and each outcome of interest. This search showed that in non-surgical patients, falls are associated with greater functional dependence.^7^
^8^ In addition, preoperative frailty and geriatric syndromes, which are linked to falls, are associated with postoperative complications^9–14^ and readmission.^15^
^16^ Together, these findings suggest that falls before surgery may presage worse surgical outcomes. However, replication in a larger study is needed.

An additional literature search was performed to identify important confounders for each proposed outcome. Searches consisted of PubMed MeSH for each outcome, along with the MeSH, ‘Risk Factors’, in order to generate a thorough search. Variables that were strongly associated with the outcomes and that would be available to clinicians during preoperative assessment were included as confounders. In addition to confounders from the literature, our previous study on preoperative falls^17^ guided selection of confounders for postoperative falls. That is, variables with ORs of 1.5 or higher were included.

### Justification

This study is highly feasible since patients have been enrolling as part of the Systematic Assessment and Targeted Improvement of Services Following Yearlong Surgical Outcomes Surveys (SATISFY-SOS) study since July 2012.^18^ Questions about falls were added to the surveys on 29 October 2013. This information is currently available for abstraction.

As noted by our review article,^3^ postoperative falls are important yet have received relatively little attention. The review also concluded that many postoperative falls most likely occur beyond the hospitalisation period, and prospective design is most likely superior to retrospective design. Using both prospective design and an extensive follow-up period, this will be the first robust observational study to characterise postoperative falls in an unselected surgical population. Characterising features of postoperative falls such as their rate of occurrence, timing, injuries and risk factors will help raise awareness of this issue and assist clinicians in designing interventions to prevent them.

The preliminary research described above suggests that a history of preoperative falls may help predict adverse surgical outcomes. Nevertheless, the history of preoperative falls is not routinely assessed. Building on preliminary work in this area, this study offers replication and generalisability, which are needed to usher change into clinical practice. If our hypothesis is confirmed, preoperative falls will become an invaluable tool in improving preoperative decision-making and postoperative care.

## Specific aims

*Aim 1*: Describe characteristics of postoperative falls in an unselected surgical population, including their rate, timing, associated injuries and risk factors.

We hypothesise that the occurrence, injuries and risk factors of postoperative falls will be similar to those of preoperative falls, and the rate of postoperative falls will decline from 30-days after surgery to 1 year after surgery.

*Aim 2a*: Determine whether a preoperative history of falls serves as a useful tool for predicting falls in the 30 days (primary outcome) and 1 year following surgery of all types.

*Aim 2b*: Determine whether a preoperative history of falls predicts patient-centred outcomes including functionality and quality of life at 30 days and 1 year after surgery (secondary outcomes).

*Aim 2c*: Replicate findings that a preoperative history of falls predicts in-hospital surgical complications and readmission at 30 days (secondary outcomes).

We hypothesise that a history of preoperative falls will predict poor postsurgical outcomes, including postoperative falls, functional dependence, poor quality of life, in-hospital complications and readmission.

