## Statistical considerations

### Sample size calculations

The required sample size is calculated based on the primary outcome, which is a fall within 30 days of surgery. Appropriate logistic regression models contain at least 10 ‘events’ per predictor variable.^20^ Since our prespecified model for postoperative falls includes 13 dependent variables (see the Analysis section), a sample with at least 130 events is required. In our population, preliminary work shows that ∼10% of patients report falling in the month following surgery. Thus, the minimum sample size needed for this study is 1300 patients.

Currently, our database contains over 9000 complete records (ie, baseline and 30-day survey) after the 16 January 2014 start date. To meet statistical assumptions of independent observations, we estimate that ∼600 records from patients with at least one previous entry in the data set will be excluded. We estimate that an additional 600 records will be excluded due to inappropriate time intervals (baseline survey to surgery <0 or >59 days; surgery to 30-day survey <20 or >120 days; or surgery to 1-year survey <275 or >455 days). Thus, our final sample size will be ∼7800.

Within this final sample, two versions of the 30-day (V.2 and V.3) and 1-year surveys (V.1 and V.2) were administered. Only V.3 of the 30-day survey and V.2 of the 1-year survey contain a validated falls question, as recommended by the Prevention of Falls Network Europe consensus group.^21^ The difference in question phrasing caused statistically significant differences in the percentage of patients reporting postoperative falls (5.5% vs 10% at 30 days and 18% vs 28% at 1-year, p<0.001). Out of the available records, about 20% (1500) completed V.3 of the 30-day survey, which is more than the 1300 required for the primary outcome. Thus, to maximise outcome validity, only these versions will be used for postoperative falls. In contrast, the readmission question contained only minor differences (‘Were you readmitted to the hospital?’ for V.2 vs ‘Check all that apply […] admitted to a hospital’ for V.3). The percentage reporting readmission was similar between surveys (5.2% vs 5.7%, p=0.416), so the results from both versions will be combined. The remaining outcomes were identical and will use all available data from both versions of the 30-day and 1-year surveys.

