Comparing patients who reported falling preoperatively with those who did not, a sample size of 1500 has 80% power to detect a 58% increase in postoperative falls within 30 days. The estimated percentage of patients who experience functional decline in the month following surgery is 20%.^22^ Our own data suggest that the SD for quality of life is 11, 28% of patients experience in-hospital complications, and 5.5% of patients are readmitted within 30 days. Thus, a sample size of 7800 patients has 80% power to detect a 15% increase in functional decline after surgery, a 0.8 point difference in physical and mental qualities of life, a 12% increase in in-hospital complications, and a 34% increase in 30-day readmission. All of the above calculations used two tails, α=0.05 and a baseline fall proportion of 26%.^17^

The minimum important difference will be a 20% difference in proportions or ORs.^23^ From the calculations above, the detectable effect sizes for falls and readmission are larger than this prespecified threshold. However, the results of interest are the ORs from regression models rather than crude bivariate analysis. For quality of life estimates, the minimum important difference will be five points.^24^
^25^

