### Analysis

To begin analysis, we will perform descriptive statistics of all variables used in the analysis, using means, SDs and Student's t-tests for normal, continuous variables; medians, IQRs and Mann-Whitney tests for non-parametric, continuous variables; and proportions and χ^2^ tests for categorical variables. We will explore and report differences between patients with follow-up surveys at 30-days compared with non-responders.^26^ Among patients included in the analysis, we will also explore and report differences between those with complete records versus those with missing data. For variables with missing data, we will perform multiple imputation where appropriate.

Our first aim is to describe the characteristics of postoperative falls in an unselected surgical population, such as their occurrence, timing, injuries and risk factors. To achieve that goal, we plan to perform the following analyses:
Descriptive statistics:
Per cent who fell while still in the hospital;Number of falls (0, 1, 2, 3+) and fall rate in the 30 days and 1-year following surgery;Fall rate and per cent who fell by surgery type (10 surgery departments);Injuries from falls in the 30 days following surgery;Injuries from falls in the 1 year following surgery.▸χ^2^:
Proportion with any injury, comparing preoperative falls to postoperative falls at 30 days and 1 year;Proportion with severe injury, comparing preoperative falls to postoperative falls at 30 days and 1 year.Risk factors: see results from logistic regression model in Aims 2a–c.

As a subaim of Aim 1, we also plan to explore the rate of falls in the short-term versus long-term postoperative periods. To accomplish this, we will calculate the rate of falls per 100 person-years in the Behavioral Risk Factor Surveillance System (BRFSS) system, which serves as the control rate of falling in the general population of adults in the USA. We will then convert the 30-day, 6-month and 1-year fall rates from the SATISFY-SOS population into falls/(100 person-years) using the BRFSS distribution. Finally, we will compare the observed rate of falling to the general population's rate of falling at 1 month and 1 year (Student's t-test) to estimate how the rate of falls changes after surgery.

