Presence or absence of at least one fall in the 30 days (primary outcome) and 1 year following surgery:
Physical activity level (<4 vs >4 metabolic equivalents (METs));Baseline altered elimination (bowel or bladder);Baseline mobility abnormality;Dizziness/vertigo;Depression.▸Barthel Index that is worse than baseline, at 30 days and 1 year after surgery:
Baseline Barthel Index score;Neurological impairment;Mood disorder (depression or anxiety);Smoking status.▸Physical quality of life score, at 30 days and 1 year after surgery:
Baseline physical quality of life score;Preoperative physical activity level (<4 vs >4 METs);Chronic pain;Mood disorder (depression or anxiety);Smoking status.▸Mental quality of life score, at 30 days and 1 year after surgery:
Baseline mental quality of life score;Chronic pain;Mood disorder (depression or anxiety).▸Presence or absence of any complication that occurred in the hospital, as reported in the 30-day survey:
Smoking status.▸Presence or absence of readmission at 30 days, as reported in the 30-day survey:
In-hospital complications (30-day survey);Incontinence.

After running each model, we will substitute the number of falls (0, 1, 2, 3+) explanatory variable for the falls and fall injuries composite scale^27^ to evaluate which scale better predicts outcomes. Since we test multiple hypotheses, the threshold for significance will be α=0.01. We will report results using ORs and 99% CIs, along with variance estimates for regression parameters.

Using SAS/STAT software, V.9.4 (SAS Institute, Cary, North Carolina, USA), [name] will perform all analyses. Analysis will begin only after acceptance of this protocol for publication. This approach reassures readers that key analyses were truly prespecified rather than post hoc. If the authors decide to perform post hoc analyses, these will be described as such and will be performed for the purpose of further hypothesis generation.

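### Aim 1 hypothesises that fall injuries are similar before and after surgery, but the only test named for injuries is a χ² difference test, which cannot support similarity and is weak at 30 days unless injury is common

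*Protocol article*

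**What the plan says.** Under Specific aims, Aim 1 is to describe postoperative falls. A hypothesis is attached to it: "We hypothesise that the occurrence, injuries and risk factors of postoperative falls will be similar to those of preoperative falls".

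Under Analysis, the Aim 1 list has descriptive items and then a χ² heading with two entries: "Proportion with any injury, comparing preoperative falls to postoperative falls at 30 days and 1 year" and "Proportion with severe injury, comparing preoperative falls to postoperative falls at 30 days and 1 year". No other inferential method is named for injuries.

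Later in Analysis, after the Aim 2 models and with multiple hypotheses as the reason, the article says that "the threshold for significance will be α=0.01". The next sentence commits to ORs with 99% CIs.

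Under Sample size calculations, the sample with usable 30-day falls data is limited: "about 20% (1500) completed V.3 of the 30-day survey", and "only these versions will be used for postoperative falls". The same section sets a threshold of importance: "The minimum important difference will be a 20% difference in proportions or ORs". It does not link that threshold to the injury comparisons, and none of its power statements covers them.

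**The concern.** The null hypothesis of a χ² test is equality. A significant result is evidence against similarity; a non-significant one is only a failure to find a difference. The injury hypothesis is therefore paired with an analysis that can never provide support for it, and the article gives no other criterion.

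This would matter less if the test were sensitive, because a miss would then make an important difference unlikely. At 30 days it is not sensitive unless injury is common. A strict α, meant to limit false positives, makes a non-significant result more likely still. What is at stake is a published statement that postoperative falls are about as injurious as preoperative ones when the data could not have told otherwise. The Justification section says that describing injuries and other features of these falls should help clinicians design preventive interventions.

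**Working it through.** **Inputs from the article (Sample size calculations)**
- 30-day fallers: 10% × 1500 = 150.
- Preoperative fallers: 26% × 1500 = 390 if restricted to the same patients, or 26% × 7800 = 2028 in the full sample. The article does not say which, so both are shown.
- Important difference: 20%, read as relative. The article calls detectable increases of 58% (falls) and 34% (readmission) larger than this threshold, yet in absolute terms they are only about 5 and 2 points.

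**Assumption.** The proportion of fallers injured is not given. The main range is 10%, 30% and 50%, with higher values checked below.

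**Method.** Normal approximation to the two-proportion test, groups treated as independent, as in an ordinary χ² test:

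power ≈ Φ[(|p₁ − p₂| − z·SE₀) / SE₁], plus a negligible opposite tail.

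SE₀ uses the pooled proportion, SE₁ the separate proportions, and z = 2.576 (α=0.01) or 1.960 (α=0.05), two-sided.

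**Reproducing the article's own figure.** It states 80% power for a 58% increase in 30-day falls with N=1500, two-sided α=0.05. With 1110 non-fallers, 390 preoperative fallers and 10% falling overall, the rate in non-fallers is 0.10 / (0.74 + 0.26 × 1.58) = 0.0869, and in fallers 0.1373. Then SE₀ = 0.01766, SE₁ = 0.01937 and power = Φ[(0.0504 − 1.960 × 0.01766) / 0.01937] = 79%. The method agrees with the article.

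**Injury comparison, one case in full.** 30% of 390 preoperative fallers and 36% of 150 postoperative fallers injured, α=0.01. Pooled proportion 0.3167, SE₀ = 0.0447, SE₁ = 0.0455. Power = Φ[(0.06 − 2.576 × 0.0447) / 0.0455] = Φ(−1.21) = 11%, so the difference is missed 89% of the time.

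**Chance of missing a true 20% relative increase (2028 to 390 preoperative fallers)**

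| Preoperative fallers injured | α=0.01 | α=0.05 |
|---|---|---|
| 10% | 95-97% | 86-89% |
| 30% | 84-89% | 66-73% |
| 50% | 59-69% | 34-45% |

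**Where it stops holding.** At α=0.01, power is 51-64% at 60% injured and 80-90% at 70%. If the 20% is read as an OR of 1.2, power at α=0.01 is 2-7% at every proportion from 5% to 70%.

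**Could the 30-day data show similarity within ±20%?** If the true proportions are equal, the SE of the log ratio is √[((1 − p)/p)(1/150 + 1/n)].

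| Injured | n | 90% CI for ratio | 98% CI for ratio |
|---|---|---|---|
| 10% | 390 | 0.62-1.61 | 0.51-1.96 |
| 10% | 2028 | 0.66-1.52 | 0.55-1.80 |
| 50% | 390 | 0.85-1.17 | 0.80-1.25 |
| 50% | 2028 | 0.87-1.15 | 0.82-1.22 |

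These intervals assume an observed ratio of exactly 1. Allowing for sampling error, the chance that two one-sided tests succeed with a 20% relative margin, when there is truly no difference, is:
- one-sided 5%: 0% up to 30% injured, 34-53% at 50%, 63-79% at 60%;
- one-sided 1%: at most 3% up to 50% injured, 18-43% at 60%.

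**The case against.** **No passage says that a non-significant χ² will be read as confirming similarity.** This stands. A reader might infer such a rule because a similarity hypothesis is followed only by a difference test, but the article does not state it. Aim 1 is labelled descriptive, and injuries are neither the primary nor a named secondary outcome. What remains is that a hypothesis and its test are both stated and do not match.

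**The α=0.01 sentence sits in the Aim 2 text, next to a commitment to 99% CIs.** This also stands: if the α governs Aim 1, the intervals arguably do too, and then only the criterion for similarity is missing. The point does not need α=0.01, since at α=0.05 the miss rate is still 66-89% for 10% to 30% injured.

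**The injury proportion is unknown.** A reader might infer that the test will usually miss the difference for injuries in general. The document does not support that: at about 60% injured or above, the difference is detected about half the time or more, and any injury could be that common.

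**The hypothesis is not unfalsifiable.** A reader might infer this for severe injury, but with 10% injured and α=0.01 a doubling would be detected with 69-84% power. The weakness is for smaller differences.

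**The 20% threshold is borrowed.** It was set among the Aim 2 outcomes and is not automatically an equivalence margin. It serves here as the article's only stated benchmark for proportions.

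**The sample could be larger.** Adding fallers from the other survey version, against the stated rule, gives about 497 (150 + 5.5% × 6300). Power at 30% injured and α=0.01 would then be only 24-51%.

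**Conclusion.** The point holds in limited form. The named analysis cannot support the injury part of the Aim 1 hypothesis, and this follows from the text without any calculation. The size of the problem at 30 days depends on the assumed injury proportion. For 10% to 50% injured, a 20% relative increase would be missed 59-97% of the time at α=0.01 and 34-89% at α=0.05. Severe injury is a subset of any injury, so its proportion is lower and it is the comparison most exposed.

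The figures rest on 150 thirty-day fallers, 390 to 2028 preoperative fallers, the relative reading of the 20%, and independent groups. The last is an approximation, since some patients fall both before and after surgery. Nothing is claimed about 1-year power, because the number of respondents to the validated 1-year version is not given. The primary and secondary outcomes are unaffected.

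**What to change.** For the Aim 1 injury comparisons:
- Report the ratio or difference of proportions, postoperative versus preoperative, with its CI, and state that a non-significant χ² is not evidence of similarity.
- Conclude that injuries are similar only if the CI lies within a stated margin, and otherwise report different or inconclusive. The 20% minimum important difference is available, but it must be explicitly adopted for Aim 1, with the relative scale and the CI level named (90% for two one-sided tests at 5%, 98% at 1%).
- State in advance that the 30-day severe-injury comparison is descriptive.

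The cost is a few sentences and intervals from the same tables; no new data are needed. The downside is that at 30 days the answer will usually be inconclusive, for severe injury and also for any injury unless its proportion is well above 50%.

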Aim 2 explores whether a preoperative history of falls serves as a useful tool for predicting surgical outcomes. First, we will calculate a crude dose–response relationship between the number of falls at baseline (0, 1, 2, 3+) and each outcome (postoperative falls, postoperative functional dependence, postoperative quality of life, in-hospital complications and 30-day readmission). For comparison, we will also calculate the crude dose–response relationship for a falls and injuries composite scale.^27^ We will examine the bivariate relationship between preoperative falls and each complication subcategory (heart/stroke, lung, blood clots, kidney/intestine, nerve injury, infection, delirium or other) using χ^2^ tests for the purpose of hypothesis generation.

To assess the relationship after controlling for important confounders, we will use logistic regression (categorical outcomes) and linear regression (continuous outcomes). Specifically, we will use forced entry of all prespecified variables. We will check all models for linearity of logit, multicollinearity, influential cases, conformity to linear gradients and goodness of fit. Since the number of possible interaction terms is large (between 45 and 91 per model), including all of them creates an unacceptably large risk of type I error. Therefore, our statistical consultant ([name]) recommended selecting only 10% of the most clinically relevant interaction terms. Using a combination of prior research and clinical judgement, two investigators ([name] and [name]) selected the 10% most clinically relevant interaction terms for each model. The online supplementary material contains these prespecified interaction terms. Non-significant interaction terms (p>0.01) will be removed from the model.

10.1136/bmjopen-2016-011570.supp8Supplementary data

Each model will include the following demographic and explanatory variables: age, sex, race (white vs non-white), BMI, preoperative falls history (0, 1, 2, 3+), Charlson Comorbidity Index (≥3 vs <3), American Society of Anesthesiology (ASA) physical status (≥3 vs <3) and procedural cardiac risk. On the basis of a careful literature search of each outcome variable (see the Literature search and review section), we selected confounding variables that are both routinely collected and known at the time of surgery planning. Outcome variables and their corresponding outcome-specific confounders are listed below.

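### Aim 2 asks whether fall history is a useful predictive tool, but the plan judges it on adjusted odds ratios and specifies no measure of discrimination or of predictive gain

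*Protocol article*

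**What the plan says.** All references are to the protocol article.

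- **The question.** Under Specific aims, Aim 2a is to "Determine whether a preoperative history of falls serves as a useful tool for predicting falls in the 30 days (primary outcome") and at 1 year. The Analysis section repeats this for the whole aim: "Aim 2 explores whether a preoperative history of falls serves as a useful tool for predicting surgical outcomes". The Justification section attaches a practical consequence. If the hypothesis is confirmed, "preoperative falls will become an invaluable tool in improving preoperative decision-making and postoperative care".
- **The quantity that answers it.** Under Sample size calculations, "the results of interest are the ORs from regression models rather than crude bivariate analysis". The same section sets the importance threshold: "The minimum important difference will be a 20% difference in proportions or ORs", with five points for quality of life.
- **The reporting.** The Analysis section sets α = 0.01 and states: "We will report results using ORs and 99% CIs, along with variance estimates for regression parameters". Its model checks are linearity, multicollinearity, influential cases, gradients and goodness of fit.
- **Related analyses.** A crude dose–response by number of prior falls (0, 1, 2, 3+) is planned for each outcome. After each model is run, the fall count is exchanged for a falls-and-injuries composite "to evaluate which scale better predicts outcomes". No criterion for that comparison is given.

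**The concern.** A variable can be independently associated with an outcome and still separate patients poorly. An adjusted odds ratio with its confidence interval shows whether fall history carries information beyond the forced-in covariates. It does not show how many future fallers the question would identify, how many patients it would flag needlessly, or how much better the model ranks patients once it is included.

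The protocol ties its result to preoperative decision-making, so this matters. A result could pass both stated thresholds (α = 0.01 and a 20% difference) and be presented as confirming a useful tool, with nothing in the planned reporting to show that discrimination is modest. The two-scale comparison has a related weakness: with no criterion fixed, one would have to be chosen later, although the Analysis section presents its key analyses as prespecified.

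**Working it through.** **Inputs** (Sample size calculations): N = 1500 for the primary outcome; 26% with a preoperative fall; about 10% falling within 30 days; detectable increase 58% (risk ratio, RR, 1.58) at 80% power, two-sided α = 0.05. The Analysis section uses α = 0.01.

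**Step 1. Reproduce the plan's figure.** Groups: 0.74 × 1500 = 1110 without and 0.26 × 1500 = 390 with a prior fall. Taking 10% as the overall risk:

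- p0 = 0.10 / (0.74 + 0.26 × 1.58) = 0.10 / 1.1508 = 0.0869
- p1 = 1.58 × 0.0869 = 0.1373

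A two-proportion test (pooled variance, no continuity correction) has 79.2% power here, and the RR detectable with exactly 80% power is 1.587. The stated 58% reproduces. If 10% is instead the risk in those without a prior fall, the detectable RR is 1.54.

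**Step 2. Turn that effect into predictive performance** for crude any-versus-no prior fall:

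- Sensitivity = 0.26 × 0.1373 / 0.10 = 0.357
- 1 − specificity = 0.26 × 0.8627 / 0.90 = 0.249, so specificity = 0.751
- PPV = p1 = 13.7%; risk without a prior fall = p0 = 8.7%, so NPV = 91.3%
- AUC of a binary predictor = (sensitivity + specificity) / 2 = (0.357 + 0.751) / 2 = 0.554

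In 1500 patients, 390 would be flagged and about 54 of them would fall (390 × 0.1373). About 96 of the 150 fallers would not be flagged.

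**Step 3. Vary the effect size** (26% exposed, 10% overall risk, crude and binary):

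| Effect | AUC |
|---|---|
| RR 1.20 (20% difference in proportions) | 0.520 |
| OR 1.2 (20% difference in ORs) | 0.518 |
| OR about 1.60 (smallest crude OR reaching p < 0.01 at N = 1500) | 0.549 |
| RR 1.58 (OR 1.67) | 0.554 |
| RR 1.74 (detectable with 80% power at α = 0.01) | 0.566 |
| OR 2 | 0.574 |
| OR 3 | 0.622 |
| OR 5 | 0.683 |

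For the secondary binary outcomes (N = 7800, α = 0.05), the detectable effects give crude AUCs of about 0.52 (functional decline), 0.52 (complications) and 0.53 (readmission).

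**Step 4. Allow for four levels.** The protocol does not give the distribution over 0, 1, 2 and 3+ falls. Under an assumed split of 74 / 13 / 6.5 / 6.5%, per-level ORs of 1.2, 1.3 and 1.5 give AUCs of 0.537, 0.555 and 0.590.

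**Step 5. Is the remedy estimable?** With 150 fallers and 1350 non-fallers, the standard error of the binary-predictor AUC is ½ × √(0.357 × 0.643 / 150 + 0.751 × 0.249 / 1350) = 0.020. The 95% interval is about ±0.04, so existing data suffice for a usable estimate.

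**The case against.** The strongest reply is that the plan contains more than odds ratios. Quality of life is analysed by linear regression with its own five-point threshold. Variance estimates are promised, and goodness of fit is checked. The crude dose–response would give the observed risk at each fall level, from which predictive values for any prior fall can be worked out. A reader might infer that the plan reports nothing but odds ratios; it does not.

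Nor is the adjusted coefficient silent on added value. It is tested in a model that forces in age, ASA status, Charlson Index and, for falls, mobility, elimination, dizziness and depression. That tests whether fall history carries information beyond them. A likelihood-ratio test with and without falls would address the same hypothesis. Only the size of the gain is missing.

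A reader might also infer that odds ratios will decide between the two fall scales, or that the plan cannot decide at all. The protocol says neither; comparing model fit is a natural reading. What stands is that no criterion is named.

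Finally, much of the article speaks of exposure, confounders and association, and the Justification claim is not tied to any analysis rule. That is fair, and it is why rewording is an acceptable remedy. It does not remove the mismatch: Aim 2a and the Analysis section both ask about a useful tool, while the protocol itself fixes odds ratios as the results of interest and an importance threshold based on association. This is therefore more than detail left to an analysis plan.

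**Conclusion.** The point holds as a mismatch between question and reported quantity. Aim 2 asks about usefulness for prediction. The plan answers with independent association and has no measure of discrimination or of predictive gain. On the protocol's own figures, an effect of the size it is powered to detect, which would exceed both of its thresholds if observed crudely, corresponds to an AUC of about 0.55, sensitivity 36% and specificity 75%, with fall risk 13.7% against 8.7%.

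These figures assume a crude, dichotomised fall history, 26% exposed and a 10% overall risk, at a detectable effect rather than an expected one. An adjusted odds ratio does not convert directly to an AUC, and the full model's AUC would be higher than that of fall history alone. A reader might infer that fall history will discriminate poorly. The documents do not support that: the four-level variable or a larger true effect would do better (0.62 at an OR of 3). What is shown is that success under the stated criteria is compatible with weak discrimination and that the planned results would not bring this out. The regressions remain valid as analyses of association; the claim of usefulness does not follow from them.

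**What to change.** Either align the analysis with the aim, or the aim with the analysis.

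1. For each binary outcome, report the c-statistic of the prespecified model with and without preoperative falls (removing any retained interaction that involves falls), and the optimism-corrected change with a confidence interval. For quality of life, report the change in R².
2. Report sensitivity, specificity, PPV and NPV of any prior fall for each binary outcome.
3. Name one criterion, AIC or the c-statistic, for comparing the fall count with the falls-and-injuries scale, and fit both to the same patients.
4. Base any conclusion that fall history is a useful tool on items 1 and 2, not on the odds ratio's p-value.

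If these are not wanted, reword Aim 2 and the claim in the Justification section as association.

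The cost is a few extra outputs from models already being fitted, with no new data. The drawback is that the headline may be less favourable.
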